### Sample Size Calculation and Power Analysis

According to G*Power 3.1.9.7 [49], when we conducted a power analysis of comparing 2 groups (ie, an intervention group and a control group), an independent *t* test for estimating a sufficient sample size with a 1-tail hypothesis, at a power of 0.80, an alpha level of 0.05, and a medium-large effect size (*d*=0.65-0.70), each group will need to include 26 to 30 participants. The estimated total sample size is 52 to 60 participants. The effect size of 0.65 to 0.70 is based on the large effect sizes (*d*>0.70) of previous internet-based intervention studies [30-35]. When a condition (intervention vs control) is a between-subjects factor and time is a within-subjects factor, a power analysis of a repeated measures within-between interaction (eg, 2 conditions × 3 times) at a power of 0.80, an α level of 0.05, a medium-large effect size (*f*=0.25-0.40), and estimated 8 measures, each group will need to include 8 to 16 participants. The effect size of 0.25 to 0.40 is based on the large effect sizes (ηp^2^>0.14) of previous internet-based intervention studies [30-35]. Therefore, the total sample size of 60 (30 for the intervention group, 30 for the control group) participants is sufficient for the proposed study. In addition, using a wait-list group as a control group is recommended for developmental trials [50].

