### Statistical Analysis

Research assistants will monitor survey completion and accelerometer data sufficiency. When participants return their survey and accelerometers, research assistants will check whether the participants have not responded to the entire survey. If there are missing responses, research assistants will email or call the participants to encourage them to respond to the missing items. The participants will be reminded twice, once each at 2 and 4 weeks, after they return the survey. If their accelerometers do not record valid data, research assistants will contact the participants and ask if they are willing to wear it for 7 days. After those attempts, when we curate the data, we will code missing data as 999.

Our analytic approach will use an intention-to-treat framework, and mixed models will yield unbiased results if the data are “missing at random” [68]. Additional sensitivity analyses will be performed to test for informative dropouts [68]. We will apply pattern-mixture models by stratifying our data by dropout patterns and fitting separate regression models to strata [68]. SPSS 26 (IBM Corp) will be used to conduct descriptive analyses (means, standard deviations), chi-squared tests, independent *t* tests, paired *t* tests, repeated measures ANOVAs, and 2-way (any 2 factors of conditions, disability severity levels, and time) and 3-way (conditions × disability severity levels × time) mixed model ANOVAs. Conditions and disability severity levels are between-subjects factors. Time is a within-subjects factor. We will use 2-way and 3-way ANOVAs to compare measured variables of the intervention and control groups. The significance level is set at .05. We will examine effect sizes of partial ηp2 (0.01, 0.06, and 0.14 as small, moderate, and large effect sizes, respectively) and Cohen *d* (0.20, 0.50, and 0.80 as small, moderate, and large effect sizes, respectively) [69]. We hypothesize that the intervention group will have stronger motivation and self-regulation, more PA, and better health conditions than the control group.

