## Results

The study was funded in April 2018. We conducted peer coach selection interviews from July 2018 through October 2018. Peer coaches codeveloped and evaluated each module of the online program from November 2018 through January 2020. We iteratively revised the modules based on the peer coaches’ feedback. During the pandemic, participants preferred to discontinue the study. The modules also had to be migrated from the Moodle system to a new online learning system, Canvas, in 2022 due to changes in the university’s online learning system.

We invited peer coaches to review the accessibility of online modules in fall 2022. We finalized the module accessibility and trained peer coaches on how to use the online modules in December 2022. Since February 2023, we have recruited 50 participants to the trial who have been assigned to the intervention group (n=25) or control group (n=25). During the follow-up stage, 3 participants dropped out of the intervention group, and 4 participants dropped out of the control group. Enrollment ended in 2024, and data collection is expected to conclude by December 2025, with results anticipated to be published in January 2026.

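### The claim that the sample is sufficient rests on a one-tailed t test at 52 to 60 participants; enrolment closed at 50, and the ANOVA calculation beside it assumes a larger effect

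*Protocol article*

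**What the plan says.** The Sample Size Calculation and Power Analysis section of the protocol article gives two calculations.

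- **Independent t test.** It seeks a "sufficient sample size with a 1-tail hypothesis, at a power of 0.80, an alpha level of 0.05", with d of 0.65 to 0.70. The result is that "each group will need to include 26 to 30 participants" and "The estimated total sample size is 52 to 60 participants". No dropout allowance is stated.
- **Repeated measures within-between interaction.** With f of 0.25 to 0.40, power 0.80, alpha 0.05 and 8 measures, it asks for 8 to 16 in each group. No correlation between repeated measures is given.

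It then concludes: "Therefore, the total sample size of 60 (30 for the intervention group, 30 for the control group) participants is sufficient for the proposed study".

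The Statistical Analysis section sets significance at .05 without naming a side. It lists independent t tests among other methods, and for the arm comparison it says: "We will use 2-way and 3-way ANOVAs to compare measured variables of the intervention and control groups". It adopts an intention-to-treat framework with mixed models.

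The Results section reports: "we have recruited 50 participants to the trial who have been assigned to the intervention group (n=25) or control group (n=25". During follow-up, "3 participants dropped out of the intervention group, and 4 participants dropped out of the control group". It also says that enrolment ended in 2024. The Recruitment and Participant Selection section still describes recruiting 60.

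**The concern.** The figure of 60 comes from the t-test calculation, since the other one asks for far fewer. That calculation has no slack: at d = 0.65 it needs all 60, one-tailed, with nobody lost. Three features of the same article pull away from it. The arm comparison is mainly by F tests, which reject in either direction. The sample that closed is smaller than the smallest size the section names. Seven participants have since dropped out. The interaction calculation appears to give comfort, but only if its effect size describes the same treatment effect as the t test's.

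At stake is how a non-significant result will be read. A reader who takes the sufficiency statement at face value would give a null result more weight than the sample supports.

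**Working it through.** **1. Inputs.** From the sample size section: alpha 0.05, power 0.80, one tail, d = 0.65 to 0.70, f = 0.25 to 0.40, 8 measures. From Results: 25 + 25 enrolled; 25 − 3 = 22 and 25 − 4 = 21 remaining, 43 in all. From Data Collection: four assessments plus an optional fifth.

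**2. Reproduce the t-test figure.** Noncentrality is δ = d·√(n₁n₂/(n₁+n₂)); power is the chance that a noncentral t with n₁+n₂−2 df passes the critical value.

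- d = 0.65, 30 per arm: δ = 0.65·√15 = 2.517, one-tailed critical value 1.672, power 80.0%.
- d = 0.70, 26 per arm: δ = 0.70·√13 = 2.524, critical value 1.676, power 80.1%.

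So 26 to 30 per arm reproduces exactly, one-tailed. Two-sided, the same inputs need 39 per arm (d = 0.65) or 34 (d = 0.70), totals of 78 or 68.

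**3. Same formula at the actual sizes.**

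| Sample | One-tailed, d = 0.65 / 0.70 | Two-sided, d = 0.65 / 0.70 | d detectable with 80% power, two-sided |
|---|---|---|---|
| 30 + 30 (target) | 80.0% / 85.0% | 69.7% / 76.0% | 0.74 |
| 25 + 25 (enrolled) | 73.3% / 78.7% | 61.5% / 67.9% | 0.81 |
| 22 + 21 (completers) | 67.4% / 73.0% | 54.8% / 61.1% | 0.88 |

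**4. The interaction calculation at its own effect.** For two arms and m time points, λ = f²·N·m/(1−ρ), with (m−1) and (N−2)(m−1) df. The article gives no ρ, so ρ = 0.5 is an assumption, with 0.3 to 0.7 as the range. At f = 0.25 and m = 3, power at N = 50 is 90.8%, 97.6% and 99.9% for ρ = 0.3, 0.5 and 0.7. At N = 43 it is 85.6%, 95.1% and 99.7%. On its own effect size this calculation survives the shortfall.

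**5. Compare the two effect sizes.** With arms equal at baseline and a difference d at every follow-up, f = (d/2)·√((1/m)(1−1/m)). With one follow-up (m = 2) this is d/4. So d = 0.65 to 0.70 is f = 0.1625 to 0.175, while f = 0.25 is d = 1.0. The two calculations do not assume the same effect.

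**6. The interaction test at d = 0.65 to 0.70.** Example: m = 4, N = 50, ρ = 0.5, d = 0.65. Then f = 0.325·√(0.25·0.75) = 0.1407, λ = 0.1407²·50·4/0.5 = 7.92, and power is 63.6%. Over m = 3 to 5 and d = 0.65 to 0.70:

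| N | ρ = 0.3 | ρ = 0.5 | ρ = 0.7 |
|---|---|---|---|
| 60 | 55-64% | 71-80% | 92-96% |
| 50 | 46-56% | 62-71% | 86-92% |
| 43 | 40-49% | 54-64% | 79-86% |

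**7. The figure of 8 to 16 in each group.** With 8 measures, two arms and ρ = 0.5, a total of 16 gives 81.8% power at f = 0.25 and a total of 8 gives 88.2% at f = 0.40. So 8 to 16 matches the total, and the per-group need is 4 to 8. Other unstated settings can produce 8 to 16 per arm (four groups with five time points at ρ = 0.5, for instance), but those are not the stated inputs. Eight measures also disagrees with the section's own example of three times and with the 4 to 5 assessments planned.

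**The case against.** Four points on the other side deserve weight.

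- **The planned ANOVA has its own calculation.** The sufficiency statement follows both calculations, and at f = 0.25 the interaction test keeps over 80% power even at 43 for ρ of 0.3 to 0.7. This stands as arithmetic. It does not rescue the claim, because that f is a larger effect than the d that sets the sample size.
- **The article never says two-sided.** Its hypotheses are directional, t tests are also planned, and an unseen analysis plan may fix the side. This stands. Two-sidedness is inferred from the F tests and a bare .05. Yet the shortfall does not depend on it: one-tailed, 25 per arm gives 73-79%, although the upper figure is within 2 points of 80%.
- **43 is a completer count.** Under intention-to-treat mixed models, participants lost during follow-up may still contribute earlier data. This stands, so the 22 + 21 figures are a floor.
- **The aim is preliminary efficacy, and effect sizes are already planned.** This softens the consequence but does not make the sufficiency statement right.

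A reader might go further and infer that the trial simply has 55-68% power. The documents do not support that as a flat statement. It is the two-sided t-test range between completers and all enrolled; the equivalence of F and two-sided t holds for a single-time contrast of two arms, and interaction power depends on a correlation that is not given. Nor is the sample size arithmetic wrong: the t-test figure reproduces exactly.

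**Conclusion.** The point holds in this form: the t-test calculation delivers 80% power at 52 to 60 participants only one-tailed and without losses, and the sufficiency statement does not carry over to the 50 enrolled. At 25 per arm and d = 0.65 to 0.70, t-test power falls short of 80% on either side, by about 1 to 7 points one-tailed and 12 to 19 points two-sided. Two-sided, even the full target of 60 falls short, at 70-76%.

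For the interaction test, 80% is reached at the 50 enrolled either at the section's larger effect (f of 0.25 or more) or, on the t test's effect, only with a high correlation of about 0.7. The interaction figures assume equal arms at baseline, a constant difference at every follow-up, 3 to 5 time points, and a correlation of 0.3 to 0.7. The two-sided t-test figures assume that the tests will not be one-tailed.

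**What to change.** In the Sample Size Calculation and Power Analysis section:

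1. Keep 60 as the planned target and state that enrolment closed at 50 (25 per arm), with 7 dropouts so far. Align the Recruitment and Participant Selection section with this.
2. Replace the sufficiency statement with power at the actual sample and the effect detectable with 80% power: two-sided d = 0.81 at 25 + 25 and 0.88 at 22 + 21, the latter labelled as a completer floor.
3. State the sidedness of the tests, here and in the Statistical Analysis section.
4. Redo the interaction calculation on the same effect as the t test, with the actual number of time points and a stated correlation (or a range), and make clear whether the result is per group or in total.
5. Report each between-arm contrast as an estimate with a 95% confidence interval, so that a non-significant result is not read as no effect.

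Recruitment is closed, so the sample and the data collection do not change. The cost is rewording, a few added figures, and a stated power less favourable than the present one.

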### Data Collection

Study assessments will be conducted at baseline, postintervention (ie, after the 8-week intervention), 3 months postintervention, 6 months postintervention, and an optional follow-up at 12 months postintervention (Figure 2). Throughout the testing phase, participants will be provided with prepaid posting labels and packages for easy access and hassle-free delivery of study material.

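### The repeated-measures sample size assumes 8 measurements the trial does not have, most likely labels totals as per-group sizes, and leaves sufficiency at f=0.25 dependent on an unstated setting

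*Protocol article*

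**What the plan says.** The section Sample Size Calculation and Power Analysis gives two calculations.

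- The first is a one-tailed independent t test with d=0.65 to 0.70, which needs 26 to 30 per group (52 to 60 in total).
- The second is a "repeated measures within-between interaction (eg, 2 conditions × 3 times) at a power of 0.80", with "a medium-large effect size (*f*=0.25-0.40") and alpha 0.05. It ends: "and estimated 8 measures, each group will need to include 8 to 16 participants".

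On the source of f, the section says "The effect size of 0.25 to 0.40 is based on the large effect sizes" of earlier internet-based studies, given as partial eta-squared above 0.14. It then concludes that 60 participants (30 per group) are enough.

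The Data Collection section sets the schedule: "Study assessments will be conducted at baseline, postintervention (ie, after the 8-week intervention), 3 months postintervention, 6 months postintervention", followed by an optional 12-month follow-up. The Results section reports 50 participants assigned (25 per group), with 7 dropouts so far. The Statistical Analysis section names SPSS 26 and partial eta-squared as an effect-size measure.

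The article does not state the correlation among repeated measurements, the sphericity correction (epsilon) or the effect-size option used in the program.

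**The concern.** Three features of the second calculation do not fit together.

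1. **Number of measurements.** One sentence contains both "eg, 2 conditions × 3 times" and 8 measures, while the schedule has four required time points and at most five. More measurements lower the required sample, so 8 is a favourable input.
2. **Unit of the answer.** Eight to 16 per group looks like program output that is really a total.
3. **Scale of the effect size.** A partial eta-squared from a repeated-measures analysis already reflects the within-person correlation. If the f derived from it is entered under the program's default option, which divides by (1 − correlation), that correlation is counted a second time and the required sample is understated.

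The t test asks for 52 to 60, and 50 were enrolled. The repeated-measures figure is therefore the only one of the two that appears to cover the achieved sample (8 to 16 against 25 per group), and readers may lean on it.

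**Working it through.** **Inputs from the article:** 2 groups, alpha 0.05, power 0.80, f=0.25 to 0.40, 8 measures, G*Power 3.1.9.7.

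**Assumed because not stated:** correlation ρ=0.5, epsilon ε=1, default effect-size option. Other values are shown below.

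**Formulas** (N = total, m = number of measurements, ε=1): the test is a noncentral F with df1 = m−1 and df2 = (N−2)(m−1).
- Default option: λ = f²·N·m/(1−ρ)
- Option matching partial eta-squared (as SPSS reports it): λ = f²·(N−2)·(m−1)

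N is raised in steps of 2 until power reaches 0.80.

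**Step 1: the printed figure (m=8, default option).**
- f=0.40: λ at N=8 is 0.16×8×8/0.5 = 20.48, power 0.882. N=6 gives 0.715. Required total: 8.
- f=0.25: λ at N=16 is 0.0625×16×8/0.5 = 16, power 0.818. N=14 gives 0.747. Required total: 16.

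The printed 8 and 16 match exactly as totals, which is 4 to 8 per group.

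**Step 2: can they be per-group sizes?** With m=8, zero correlation gives 7 to 15 per group and the partial-eta-squared option gives 8 to 18. These are close, but neither matches both ends. Varying ρ from 0 to 0.9 at 3, 4, 5 and 8 measurements gave no setting that returns exactly 16 and 32 in total. The mislabel is therefore the best-supported reading, not a proven one.

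**Step 3: the trial's own number of times.** Required totals, f=0.40 to f=0.25:

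| Times | Default, ρ=0.5 | Default, ρ=0 | Partial-eta-squared option |
|---|---|---|---|
| 3 | 12–28 | 22–54 | 34–82 |
| 4 | 12–24 | 20–46 | 26–62 |
| 5 | 10–22 | 18–40 | 22–52 |

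**Step 4: scale of f.** Partial eta-squared 0.14 converts to f = √(0.14/0.86) = 0.403, the upper planned value. The lower value, f=0.25, corresponds to 0.0625/1.0625 = 0.059.

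**Step 5: power at f=0.25.**

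| Times | N=60, default ρ=0.5 | N=60, default ρ=0 | N=60, partial-eta-squared | N=50, partial-eta-squared |
|---|---|---|---|---|
| 3 | 0.991 | 0.851 | 0.66 | 0.57 |
| 4 | 0.998 | 0.910 | 0.79 | 0.70 |
| 5 | >0.999 | 0.948 | 0.87 | 0.79 |

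**Step 6: effect detectable with 80% power at N=50, partial-eta-squared option:** f=0.32 at 3 times, 0.28 at 4, 0.25 at 5.

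**Step 7: the t test.** One-sided, it reproduces exactly: 26 per group at d=0.70 and 30 at d=0.65.

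**The case against.** The strongest reply is that none of this changes the planned number. Calling a total a per-group size doubles the stated requirement, so that slip is conservative. The article in effect asks for 16 to 32 in total, and the default-option correction at 3 to 5 times is only 10 to 28. The 60 is the upper end of the t-test range. All of this stands.

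It can also be said that the shortfall appears only at f=0.25 under one program option, that an article commonly leaves such settings to the full protocol, and that the quoted basis (partial eta-squared above 0.14) implies f near 0.40. At f=0.40 even the stricter option needs only 34, 26 or 22 in total at 3, 4 or 5 times. This stands too. But the article itself plans on 0.25 as its lower value and ties the whole range to partial eta-squared, so the matching option is a natural reading. What the cited studies' values contained cannot be checked from the document.

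Two stronger readings are tempting. A reader might infer that the claim of a sufficient sample is false. The document does not support that: under default settings 60 is ample, and it is enough even at zero correlation. A reader might also infer that 50 participants give 80% power only for effects near f=0.40. The figures contradict that: even on the stricter scale the detectable effect is 0.25 to 0.32.

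**Conclusion.** The repeated-measures sample size is mis-specified as written. Eight measurements agree neither with the 3 times in the same sentence nor with a schedule of four required assessments plus one optional; that follows from the text alone. The per-group label is most likely wrong, on the assumption of default correlation and epsilon.

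The error does not by itself overturn 60. What remains open is the lower planned effect. If f is on the partial-eta-squared scale, four assessments give power 0.79 at 60 (62 needed) and 0.70 at the 50 enrolled. If the default option truly applies, power at 60 is 0.91 or more with four assessments. Sufficiency at f=0.25 therefore turns on a setting the article does not give.

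**What to change.** - Rerun the interaction calculation with the four required assessments and remove the reference to 8 measures. Reconcile the 3-times example with the schedule.
- State the correlation, epsilon and effect-size option, using the option that matches partial eta-squared if f comes from it.
- Label total sample sizes as totals.
- Report the effect detectable with 80% power for the 50 enrolled. On the partial-eta-squared scale this is about f=0.28 at four assessments (0.32 at three).

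The cost is one rerun of the power program and a few changed sentences. The design and data collection are unaffected. If the partial-eta-squared option applies, the stated requirement becomes less favourable.

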### Recruitment and Participant Selection

Recruitment will be conducted using a purposive sampling method within the United States by publishing this trial on the National Multiple Sclerosis Society website. Once participants sign up using the sign-up sheet, or by calling or emailing the research team, the team will conduct a short telephonic interview, which involves screening the participants based on the inclusion criteria (see Textbox 1). Once participants are recruited, they will be asked to fill out the baseline survey and wear an accelerometer for 7 days. The baseline assessment materials will be sent to the participant via physical mail, with a prepaid postage packet provided to send the device back to the research lab. We will recruit 60 participants with any type of MS who satisfy the inclusion criteria (see Textbox 1).

Inclusion and exclusion criteria for participant enrollment into the trial.
**Inclusion criteria**
≥18 years old andAny type of multiple sclerosisNot maintained 30 minutes of moderate-to-vigorous physical activity (PA) per day for 2 days of the week during the previous 6 monthsRelapse-free for the past 30 daysHave a low risk of contraindications of PA indicated by no more than a single “yes” response on the Physical Activity Readiness Questionnaire (PAR-Q) [51]Able to walk with or without an assistive device (ie, Patient-Determined Disease Steps [PDDS] score from 0 to 6) [52]Be willing to be randomized to an intervention or control group, complete the surveys and questionnaires, and wear an accelerometer during the intervention periodHave reliable internet access
**Exclusion criteria**
Godin Leisure-Time Exercise Questionnaire (GLTEQ) score >14 [53]No computer nor mobile device access to the internetPDDS score=7 (ie, using a wheelchair or scooter most of the time) or PDDS score=8 (being bedridden)Anyone living outside of the United StatesAnyone who is unable to speak, read, and write in EnglishNot willing to be randomized to an intervention or control group, complete the surveys and questionnaires, and wear an accelerometer during the intervention periodNo access to reliable internet

### Randomization

Research assistants enroll participants prior to randomization. The research team, including the principal investigator and a research assistant, will conduct matched, paired randomization based on Patient-Determined Disease Steps (PDDS) scores. Randomization will be conducted by flipping a coin until there are no significant differences in PDDS, Godin Leisure-Time Exercise Questionnaire (GLTEQ), age, education levels, income, and gender. To assign qualified participants in a timely manner, we will randomize every 8 to 10 participants into the intervention or wait-list control group (Figure 1). Participants will be notified regarding their allocation via email and phone call.

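### Uncapped re-flipping of the allocation until six covariates are non-significant adds little balance, leaves discretion to the study team, and is not reflected in the named between-arm models

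*Protocol article*

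**What the plan says.** Protocol article, Randomization: "Research assistants enroll participants prior to randomization". Then "The research team, including the principal investigator and a research assistant, will conduct matched, paired randomization based on Patient-Determined Disease Steps (PDDS) scores". The acceptance rule is "Randomization will be conducted by flipping a coin until there are no significant differences in PDDS"; the same criterion is applied to five more variables, namely GLTEQ, age, education, income and gender. Allocation proceeds in small groups: "we will randomize every 8 to 10 participants into the intervention or wait-list control group".

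The section names no test, no threshold, no limit on the number of flips and no person outside the team who draws or holds the allocation. It does not say whether significance is judged within each batch or cumulatively.

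Protocol article, Statistical Analysis, names t tests, repeated measures ANOVAs, and 2-way and "3-way (conditions × disability severity levels × time) mixed model ANOVAs", and adds: "We will use 2-way and 3-way ANOVAs to compare measured variables of the intervention and control groups". Disability severity is a between-subjects factor in some of these models. No model is described with a term for pair, batch, GLTEQ as a balancing covariate, age, education, income or gender. The first sample size calculation treats the arms as independent samples.

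The Results section reports 25 assigned to each arm, 3 and 4 dropouts, enrollment ended in 2024, and data collection continuing to December 2025.

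**The concern.** Three things follow from the allocation rule as written.

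- **Balance.** Non-significance is a weak criterion for balance when the groups compared are small. A rule that almost any allocation passes does little.
- **Discretion.** A team that includes the principal investigator and a research assistant discards allocations and redraws, with no cap or stated test. The final allocation cannot be audited from what is written.
- **Analysis.** The allocation is restricted on six variables, but the named models carry at most one of them, through severity. When restricted variables predict the outcome, an analysis that omits them overstates the standard error of the between-arm difference and forgoes precision.

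At stake are the credibility of the randomised comparison and the precision of between-arm estimates in a trial that enrolled 50 rather than the planned 60.

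**Working it through.** **Inputs from the protocol article.** Batches of 8 to 10, so 4 or 5 per arm; PDDS-matched pairs; six checked variables; 25 per arm assigned; design effect d = 0.65 to 0.70, one-tailed alpha 0.05, power 0.80.

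**The plan's own figure.** One-tailed independent t test, power 0.80: d = 0.65 needs 30 per group and d = 0.70 needs 26. This reproduces the stated 26 to 30.

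**Step 1: what the check can detect.** The smallest observed standardised difference that reaches two-sided p = 0.05 with n per arm is t(0.975, 2n − 2) × √(2/n). The two-sided 0.05 threshold is my assumption.

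| Scope of check | n per arm | t | √(2/n) | Critical difference (SD) |
|---|---|---|---|---|
| Batch of 8 | 4 | 2.447 | 0.707 | 1.73 |
| Batch of 10 | 5 | 2.306 | 0.632 | 1.46 |
| All 50 at once | 25 | 2.011 | 0.283 | 0.57 |

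**Step 2: what the rule achieves.** Monte Carlo of the written procedure: pairs sorted on PDDS, and an allocation accepted only if five t tests and a Fisher test on gender all have p ≥ 0.05. Assumptions not in the documents: correlation of 0.2 between covariates, and 75% of participants in one gender category. With the check made per batch:

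- About 82% of paired allocations pass (13.2 of 16 for batches of 8; 26.3 of 32 for batches of 10).
- In accepted batches, at least one of GLTEQ, age, education and income differs by more than 0.5 SD in 86 to 90%, and by more than 1 SD in 25 to 38%.
- The variance of the final between-arm difference falls about 16 to 26% for those four variables and 3 to 10% for gender.
- For PDDS it falls 83 to 87%, but through the matching and not through the re-flip.

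Applied once to all 50, the re-flip rule cuts the variance by about 25%, which is about 13% of the SD (1 − √0.75 = 0.13).

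**Step 3: effect on the analysis.** Same simulation with 48 to 50 participants, two-sided alpha 0.05, and a baseline-to-follow-up correlation of 0.6 (assumed). R2 is the assumed share of outcome variance explained by the six variables. Each cell gives the ratio of model SE to true SE, then the type I error; ranges cover batches of 8 and 10.

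| R2 | Unadjusted t test | With two-level severity | Change from baseline (condition × time) |
|---|---|---|---|
| 0 | 0.99–1.02; 4.7–5.1% | 0.99–1.01; 4.7–4.9% | 1.00–1.01; 4.7–4.8% |
| 0.3 | 1.07; 3.3–3.8% | 1.03; 4.1–4.6% | 0.99–1.01; 4.8–5.0% |
| 0.5 | 1.12–1.16; 2.2–2.7% | 1.05–1.09; 3.1–3.8% | 0.99–1.01; 4.9–5.1% |

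Adjusting for all six variables brings type I error to about 4.4 to 5.5%, nominal within simulation error. The last column assumes covariate effects that are constant over time.

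**The case against.** The strongest reply has four parts.

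- **Steering is not shown.** Participants are enrolled before they are randomised, in batches, so a coming assignment cannot influence who enters. A rule that stops at the first acceptable flip treats the arms symmetrically and does not bias the effect. This stands. A reader might infer that the trial's effect estimate is biased; the documents do not support that. What remains is a vulnerability if the rule is not followed strictly. For scale, keeping the better of two acceptable flips per batch would shift an unmeasured prognostic variable by about 0.34 to 0.38 SD, against a design effect of 0.65 to 0.70. Nothing says this happened.
- **The matching variable is partly in the models.** Severity is a planned between-subjects factor and most naturally means PDDS, although the scale is not named there. It is therefore too strong to say that the trial is analysed as if simply randomised, or that its standard errors are wrong throughout. The mismatch arises only if the covariates predict outcome, it is conservative, and it is close to nil for condition-by-time under the assumption above.
- **The allocation does not throw power away.** With 25 per arm and d = 0.65, a two-sided t test under simple randomisation has 61.5% power (73% one-tailed). Simulated unadjusted two-sided power under the rule is about 63%. A rise to 77% with adjustment, assuming PDDS explains 25% and the other covariates 10% of variance, is a gain from covariates and not the recovery of a loss caused by allocation.
- **Detail may sit elsewhere.** A condensed article can leave the covariate list and the custody of the allocation to fuller documents. That is fair for what is unsaid. It does not cover the re-flip rule, which the article states.

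**Conclusion.** The point holds in a limited form. The re-flip rule is written as described and adds little beyond the PDDS matching under either reading of its scope: the critical difference is 1.46 to 1.73 SD per batch or 0.57 SD on all 50. It gives the team uncapped discretion over which allocation is kept. This weakens the defensibility of the randomisation without demonstrating bias.

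On the analysis side, unadjusted between-arm t tests and condition main effects are conservative to the extent that the balancing variables predict outcome: type I error is about 3.3 to 3.8% at R2 = 0.3 and 2.2 to 2.7% at R2 = 0.5, less affected with severity in the model. Those R2 values, the covariate correlations and the balance-test threshold are assumptions; at R2 = 0 there is no distortion. No inflation of false positives follows. Some prognostic value is plausible, since GLTEQ is both a balancing variable and a physical activity outcome, although the exclusion of scores above 14 narrows its baseline range.

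**What to change.** All 50 participants are assigned, so the allocation itself cannot be changed. The analysis and the reporting still can be, while data collection continues.

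1. In the between-arm models, adjust for PDDS (or pair), GLTEQ, age, education, income and gender, with batch if degrees of freedom allow. PDDS as a covariate is the practical choice: 25 pairs as a fixed factor would use 24 degrees of freedom. Where GLTEQ is the outcome and its baseline is already a time level, do not enter that baseline a second time as a covariate.
2. Report the number of discarded allocations per batch, or disclose that it was not recorded. State which test and threshold were used and whether the check was per batch or cumulative.
3. Where those facts are known, add a sensitivity randomisation test that replays the actual rule: pairs, batches, and re-flip until accepted.

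**Cost.** Plan wording and a short program; no new data. The model uses about 6 to 10 more degrees of freedom. With 43 completers (50 − 7), a two-group comparison has 41 residual degrees of freedom, which would fall to between 35 and 31. That is a real price in a small trial, and the reason batch is conditional.
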